#### Evaluation and randomization

Patients must be restaged within 4 weeks prior to randomization. The study will employ a 1:1 randomization between arm A: arm B, stratified on primary tumor histology (melanoma, renal cell carcinoma, non-small-cell carcinoma, urothelial carcinoma or head-and-neck squamous cell carcinoma) and on the number of metastases present at the time of inclusion (≤3 or > 3). Randomly permutated blocks of variable length 2 and 4 will thus be assigned to each stratum. Within each block, assignment to treatment and control is random but balanced. Every patient is assigned a treatment arm following the randomization-scheme. As this is an open-label trial, the randomization procedure and outcome will not be blinded.

#### Interventions

Arm A: interventional arm:Patient receives 1/2 cycle(s) of CPI (depending on type of CPI). Prior to the second/third cycle, SBRT is administered to maximally 3 extracranial lesions in 3 fractions of 8 Gy, for a total dose of 24 Gy on each lesion. Patient receives 3–5 cycles of CPI in total prior to first evaluation (imaging + consultation).
Simulation:All patients will receive a CT in supine position with 3 mm CT slice thickness at the level of the tumor site. The planning simulation CT should cover the target and all organs at risk (OARs). A typical scan length should extend at least 10 cm superior and inferior beyond the treatment field borders. Support devices to increase patient comfort will be chosen depending on the tumor localization. Lung and liver tumor sites will be simulated with 4D-CT, taking into account breathing. The isocenter will be determined on the CT-simulator with marking of laser lines on the patient. Imaging data will be transferred to the treatment planning system. The types of OARs delineated depend on the localization of the metastasis.SBRT target and OAR definition:Gross Target Volume (GTV): all visible tumor by combining iconographic and metabolic information (if available). No clinical target volume will be delineated.Planning Target Volume (PTV): expansion from the GTV to account for organ motion and setup error. Margins depend on the site irradiated with 2 mm margins for bony lesions and 5 mm for other sites. In case of overlap between OAR and PTV exists, a PTV_optim is created by subtracting the OAR or the planning organ at risk volume (PRV) from the PTV volume. This PTV_optim will be used to prescribe the dose instead of the PTV.A Planning Organ at Risk Volume (PRV) expansion of 2 mm will be added to the spinal cord, esophagus, intestine, etc. (if applicable), and dose constraints apply to this PRV. It is strongly recommended that dose constraints not be exceeded. If a dose constraint cannot be achieved due to overlap of the target with an OAR, the fractionation can be increased or the target coverage compromised in order to meet the constraint.SBRT treatment planning and dose prescription:IMRT (static or rotational) treatment planning will depend on the localization of the lesion. Dose constraints of OARs will be in accordance with the recommendations from the report of the AAPM task group 101 [23]. The total dose (24 Gy = 80% of the maximal dose (30 Gy)) will be delivered in 3 fractions and fractions will be separated > 48 h and < 96 h. Treatment will be prescribed to the periphery of the target (80% of the maximal dose should cover 90% of the PTV) covering the PTV. In case of violation of dose constraints to the surrounding OARs, the prescription will be adapted accordingly.SBRT delivery and verification:Treatment will be delivered with static or rotational IMRT with 6–18 MV photons of a linear accelerator using cone-beam CT set-up and on-line correction of patient’s position. If multiple targets will be irradiated and the targets are more than 10 cm apart in the cranio-caudal direction, multiple isocenters are needed with a CBCT prior to every treatment for every isocenter. Patient immobilization devices can be used according to the institutional policy.Arm B: control armPatient receives 3–5 cycles of CPI with subsequent first evaluation (imaging + consultation).

#### Duration of therapy

CPI dose adjustments according to standard of care regimens are allowed after the first evaluation at the discretion of the investigator (e.g. nivolumab q2w to q4w). Patients may discontinue protocol therapy in case of radiographic disease progression (as per iRECIST). A subject may be granted an exception to continue on treatment with confirmed radiographic progression if clinically stable or clinically improved. Patients may also discontinue protocol therapy when unacceptable toxicity is encountered, in case of intercurrent illness which would in the judgment of the investigator affect patient safety or the ability to deliver treatment; or by request of the patient.

#### Concomitant medications/vaccinations (allowed & prohibited)

Medications or vaccinations specifically prohibited in the exclusion criteria are not allowed during the ongoing trial. If there is a clinical indication for one of these or other medications or vaccinations specifically prohibited during the trial, discontinuation from trial therapy or vaccination may be required. The investigator should discuss any questions regarding this with the study coordinator. The final decision on any supportive therapy or vaccination rests with the investigator and/or the subject’s primary physician.

##### Acceptable concomitant medications

All treatments that the investigator considers necessary for a subject’s welfare may be administered at the discretion of the investigator in keeping with the community standards of medical care. All concomitant medication will be recorded on the case report form (CRF) including all prescription, over-the-counter (OTC), herbal supplements, and IV medications and fluids. If changes occur during the trial period, documentation of drug dosage, frequency, route, and date may also be included on the CRF.

All concomitant medications received within 28 days before the first dose of trial treatment and 30 days after the last dose of trial treatment should be recorded. Concomitant medications administered after 30 days after the last dose of trial treatment should be recorded for SAEs.

##### Prohibited concomitant medications

Subjects are prohibited from receiving the following therapies during the Screening and Treatment Phase (including retreatment for post-complete response relapse) of this trial:
Antineoplastic systemic chemotherapy or biological therapyImmunotherapy not specified in this protocolChemotherapy not specified in this protocolRadiation therapy, other than defined in this protocol: indications for non-study prescribed radiotherapy should always be discussed first with the study sponsor.Live vaccines within 30 days prior to the first dose of trial treatment and while participating in the trial. Examples of live vaccines include, but are not limited to, the following: measles, mumps, rubella, varicella/zoster, yellow fever, rabies, BCG, and typhoid vaccine.

#### Adverse events reporting requirements

Patients will be instructed by the investigator to report the occurrence of any adverse event (AE). The investigator assesses and records all AEs observed during the AE reporting period from inclusion until 4 months after randomization. Special attention should be given to AEs predefined on the AE-form. All AEs are coded with the CTCAE v5.0, and assigned a grade (from 1 = mild to 5 = death related to AE) as well as a relationship to trial treatment. Grade 0 = absent must be used for the absence of predefined AEs.

Serious adverse events (SAEs) will be reported within 24 h (working days) to the central and local Ethics Committees.

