## Methods/design

This study is approved by the Ghent University Hospital Ethics committee (EC2017/1678) and is registered on clinicaltrials.gov (NCT03511391). Patients diagnosed with locally advanced or metastatic melanoma, renal cell carcinoma, non-small cell lung carcinoma, urothelial carcinoma or head- and neck squamous cell carcinoma will be entered in a randomized phase II trial. In the interventional arm A, patients will undergo SBRT to maximally three extracranial lesions in addition to SOC CPI treatment. Patients in the control arm B will only receive SOC CPIs (Fig. 1).

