#### Study calendar

Baseline/pre-study evaluations:
Documentation of the patient’s medical history and all medicationRegistration of baseline symptoms/toxicity and QOLKarnofsky Performance statusClinical examinationBlood draw assessing at least the following elements: complete blood count (hemoglobin, white blood cell count and formula, thrombocyte count), electrolytes (sodium, potassium), renal function (creatinine, blood urea nitrogen), liver function (alanine aminotransferase, aspartate aminotransferase, gamma-glutamyltransferase, alkaline phosphatase), lactate dehydrogenase and C-reactive protein.

Baseline evaluations are to be conducted within 2 weeks prior to start of checkpoint inhibitors.

During study:
Registration of symptoms before first cycle of checkpoint inhibitors, at start of radiotherapy and at end of radiotherapy (if applicable) and at least every 4 weeks until 4 months after randomization. Toxicity will be assessed using the CTCAE version 5.0.QOL will be assessed at baseline, at first evaluation and every 6 months thereafter. QOL will be assessed using the QLQ-C30 questionnaire.A fecal sample will be obtained prior to start of CPI treatment and at the first evaluation.Blood samples (EDTA and serum) for immunological analysis will be obtained prior to start of CPIs, before first fraction (Arm A), before the second/third cycle of CPIs and at every evaluation (consultation after imaging) as long as patient receives CPI (i.e. liquid biopsy).Patients will be followed up until disease progression defined as per iRECIST.Off-study and follow-up evaluationsOnce a subject experiences confirmed disease progression, the subject moves into the survival follow-up phase and should be contacted by telephone every 12 weeks to assess for survival status until death, withdrawal of consent or the end of the study, whichever occurs first.Monitoring of progression and survival.

Study calendars for different CPI treatment schedules are represented in Tables 1, 2, and 3.

**Table 1 Tab1:** Study calendar for nivolumab 2-weekly: SBRT prior to C3; first evaluation after C5

	STUDY PERIOD											
	Enrolment	Allocation	Post-allocation								Close-out	Long-term follow-up
**TIMEPOINT**	**Pre-study**	**D-14 to -1**	**C1D1**	**C2D1**	**C3D-6**	**C3D-4 or -3**^**a**^	**C3D-1**	**C3D1**	**C4D1**	**C5D1**	**C5D +1 to +14**	**Every evaluation**^b^

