**INTERVENTIONS**												
SBRT fraction (arm A)					X	X	X					
Nivolumab q2w (arm A & B)			X	X				X	X	X		

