**ASSESSMENTS**												
Demographics, medical Hx, performance status	X											
Imaging (CT or PET/CT)	X										X	
Fecal sample			X								X	
Liquid biopsy			X		X^c^			X				X
Adverse events			X	X	X^c^			X	X	X	X	X^d^
Quality of life			X									X^e^

*C* cycle; *CT* computed tomography; *D* day; *Hx* history; *PET* positron emission tomography; *q2w* 2-weekly; *SBRT* stereotactic body radiotherapy

^a^ SBRT is given on Wednesday-Friday-Monday or Friday-Monday-Wednesday, depending on whether nivolumab is administered on Tuesday or Thursday, respectively

^b^ Consultation after imaging; until disease progression as per iRECIST

^c^ Only for patients in study arm A

^d^ Until 3 months after radiotherapy

^e^ At least every 6 months

**Table 2 Tab2:** Study calendar for nivolumab 4-weekly: SBRT prior to C2; first evaluation after C3

	STUDY PERIOD									
	Enrolment	Allocation	Post-allocation						Close-out	Long-term follow-up
**TIMEPOINT**	**Pre-study**	**D-14 to -1**	**C1D1**	**C2D-6**	**C2D-4 or -3**^**a**^	**C2D-1**	**C2D1**	**C3D1**	**C3D +1 to +14**	**Every evaluation**^b^

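### The text ends adverse event recording four months from randomisation in both arms, but the calendars tie it to radiotherapy, which gives arm B no end date and moves arm A's with the drug schedule

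*Protocol article*

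**What the plan says.** The protocol article gives two rules for when AE recording stops.

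- **Text.** Under Adverse events reporting requirements, the investigator records all AEs in an "AE reporting period from inclusion until 4 months after randomization". Under Study calendar, symptoms are registered "at least every 4 weeks until 4 months after randomization". Neither statement distinguishes the arms.
- **Calendars.** In Tables 1, 2 and 3 the AE cell in the long-term follow-up column (every evaluation) carries footnote d: "Until 3 months after radiotherapy".

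The tables apply to both arms: their drug rows name arms A and B. Where a cell concerns one arm only, the tables use footnote c, "Only for patients in study arm A". It marks the AE cell at the first radiotherapy fraction, but not the follow-up AE cell. The Methods/design section states that "Patients in the control arm B will only receive SOC CPIs".

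**The concern.** The two rules start from different dates and so end on different dates. Both are current text, and the footnote is the same in all three tables, so this is not a slip in a single cell.

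The footnote's anchor is an event that only arm A is scheduled to have. The Discussion allows palliative irradiation in arm B, but that is neither given to every control patient nor given at a set time, so it cannot stand in as an anchor. In arm A the footnote's end date also moves with the drug schedule and with the delay from allocation to first dose.

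Toxicity is a secondary endpoint and the trial is open-label. A site working from the calendar and a site working from the text could close AE recording on different days, and under the calendar rule the length of observation depends on the arm.

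**Working it through.** **Inputs**

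- Text window: 4 months from randomisation.
- Footnote window: 3 months from radiotherapy. The document does not say whether this means the first or the last fraction, so both are shown.
- Allocation to first dose (C1D1): 1 to 14 days (Tables 1 to 3, allocation column). Allocation is taken as the randomisation date.
- Radiotherapy timing: Table 1 is headed "Study calendar for nivolumab 2-weekly: SBRT prior to C3; first evaluation after C5" and Table 2 "Study calendar for nivolumab 4-weekly: SBRT prior to C2; first evaluation after C3"; Table 3 (three-weekly pembrolizumab or atezolizumab) also places it before C3. The first fraction is 6 days, and the last 1 day, before the named cycle.
- Conversion (assumed): 1 month = 365.25/12 = 30.44 days, so 3 months = 91.3 days and 4 months = 121.8 days.

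**Days from C1D1 to radiotherapy**

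- Nivolumab, two-weekly (C3) or four-weekly (C2): the cycle starts 28 days after C1D1. First fraction 28 − 6 = 22; last fraction 28 − 1 = 27.
- Three-weekly (C3): the cycle starts 42 days after C1D1. First fraction 42 − 6 = 36; last fraction 42 − 1 = 41.

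**End of the footnote window, in days after randomisation** = lead time (1 to 14) + days to the fraction + 91.3

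| Schedule | Counted from | End of window | Minus text (121.8) | Lead days on which footnote ends later |
|---|---|---|---|---|
| Nivolumab | last fraction | 119.3 to 132.3 | −2.4 to +10.6 | 11 of 14 |
| Nivolumab | first fraction | 114.3 to 127.3 | −7.4 to +5.6 | 6 of 14 |
| Three-weekly | last fraction | 133.3 to 146.3 | +11.6 to +24.6 | 14 of 14 |
| Three-weekly | first fraction | 128.3 to 141.3 | +6.6 to +19.6 | 14 of 14 |
| Arm B | – | not defined | – | – |

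Differences are taken before rounding. At the same lead time, the three-weekly window ends 41 − 27 = 14 days after the nivolumab window. Using true calendar months over every start date in a year gives the same picture. Counted from the last fraction, the footnote ends later in about 76% of nivolumab combinations and in all three-weekly ones.

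**Does a scheduled evaluation fall in the gap?** The follow-up column covers consultations after imaging, and imaging is every 3 months (Objectives).

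- Nivolumab: the first imaging is 1 to 14 days after a cycle that starts 56 days after C1D1. With the lead time this is day 56 + 1 + 1 = 58 to 56 + 14 + 14 = 84. About 91 days later is day 149 to 175.
- Three-weekly: the first imaging is 5 to 20 days after a cycle that starts 63 days after C1D1. This is day 63 + 5 + 1 = 69 to 63 + 20 + 14 = 97. About 91 days later is day 160 to 188.
- If the 3-month interval is counted from randomisation instead, evaluations fall near days 91 and 182.

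On either reading, none falls between day 122 and day 146.

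**The case against.** The strongest reply is that the document, read as a whole, does give arm B an end date. The text states an arm-neutral window twice, and the footnote would have to override both statements for arm B to be left open. That is right. A reader might infer that arm B has no stop date at all; the documents support only that the footnote supplies none.

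Second, footnote d sits only in the every-evaluation column, and both rules take in the same scheduled evaluations. This also stands. What can differ is AEs noted between evaluations or at unscheduled imaging. The column also ends at progression: with the control median PFS of 3.1 months from the Sample size section and an assumed exponential curve, 1 − 2^(−4/3.1) = 59% of control patients would have progressed by month 4. Fewer patients would therefore contribute any extra days.

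Third, a reader might infer unequal visit schedules, because the text adds symptom registration at the start and end of radiotherapy. That comes with giving radiotherapy. In the tables it amounts to one arm-A-only AE cell, at the first fraction. The last fraction is the day before a cycle at which both arms are assessed.

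None of this reconciles the footnote with the text.

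**Conclusion.** The contradiction is real and the footnote is wrong as printed: it applies to both arms but can be evaluated in only one. For arm A it shifts the end of AE recording by −2 to +11 days (nivolumab) or +12 to +25 days (three-weekly drugs) if counted from the last fraction. Counted from the first fraction, the shifts are −7 to +6 and +7 to +20 days. A window longer than the text's is therefore certain only for three-weekly drugs; for nivolumab it depends on the unstated starting point and on the lead time.

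A reader might turn the largest gap into an excess of about 20% in arm A's AEs (24.6/121.8), or call the toxicity comparison uninterpretable. The documents support neither. That figure needs three-weekly treatment, the full 14-day lead, counting from the last fraction, a constant AE rate, and the footnote applied in arm A while the text is applied in arm B. If every site follows the text, the windows are equal. The supported conclusion is an avoidable, probably small, source of bias in a secondary endpoint. It rests on sites being free to work from either rule and on the visit timing in the calendars.

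**What to change.** Reconcile the passages. In Tables 1, 2 and 3, replace footnote d with the window already given under Adverse events reporting requirements and Study calendar: until four months from randomisation, identical in both arms. State that AEs are compared between arms within that common window.

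The cost is one footnote in three tables, one sentence on the analysis, and a note to sites so that the case report form and local calendars agree. No visit, treatment or assessment changes, and no AE collection beyond the window in the text is needed to resolve this point.

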#### Study calendar

Baseline/pre-study evaluations:
Documentation of the patient’s medical history and all medicationRegistration of baseline symptoms/toxicity and QOLKarnofsky Performance statusClinical examinationBlood draw assessing at least the following elements: complete blood count (hemoglobin, white blood cell count and formula, thrombocyte count), electrolytes (sodium, potassium), renal function (creatinine, blood urea nitrogen), liver function (alanine aminotransferase, aspartate aminotransferase, gamma-glutamyltransferase, alkaline phosphatase), lactate dehydrogenase and C-reactive protein.

Baseline evaluations are to be conducted within 2 weeks prior to start of checkpoint inhibitors.

During study:
Registration of symptoms before first cycle of checkpoint inhibitors, at start of radiotherapy and at end of radiotherapy (if applicable) and at least every 4 weeks until 4 months after randomization. Toxicity will be assessed using the CTCAE version 5.0.QOL will be assessed at baseline, at first evaluation and every 6 months thereafter. QOL will be assessed using the QLQ-C30 questionnaire.A fecal sample will be obtained prior to start of CPI treatment and at the first evaluation.Blood samples (EDTA and serum) for immunological analysis will be obtained prior to start of CPIs, before first fraction (Arm A), before the second/third cycle of CPIs and at every evaluation (consultation after imaging) as long as patient receives CPI (i.e. liquid biopsy).Patients will be followed up until disease progression defined as per iRECIST.Off-study and follow-up evaluationsOnce a subject experiences confirmed disease progression, the subject moves into the survival follow-up phase and should be contacted by telephone every 12 weeks to assess for survival status until death, withdrawal of consent or the end of the study, whichever occurs first.Monitoring of progression and survival.

Study calendars for different CPI treatment schedules are represented in Tables 1, 2, and 3.

**Table 1 Tab1:** Study calendar for nivolumab 2-weekly: SBRT prior to C3; first evaluation after C5

	STUDY PERIOD											
	Enrolment	Allocation	Post-allocation								Close-out	Long-term follow-up
**TIMEPOINT**	**Pre-study**	**D-14 to -1**	**C1D1**	**C2D1**	**C3D-6**	**C3D-4 or -3**^**a**^	**C3D-1**	**C3D1**	**C4D1**	**C5D1**	**C5D +1 to +14**	**Every evaluation**^b^

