## Statistical analysis

### Sample size

This trial is designed to assess whether SBRT to maximum 3 lesions after 2 cycles of CPIs could prolong PFS as compared to standard of care in metastatic patients. The study has a two-sided 0.05% type I error and 80% power to detect an improvement in PFS of 3 months in the intervention group as compared to the control group using a stratified log-rank test. Median PFS for the control arm was estimated at 3.1 months. Median PFS after initiation of CPIs is approximately as follows:
20% metastatic melanoma (1st-3rd line): 5.2 months [1, 4, 24–26]20% renal cell carcinoma (2nd line): 4.6 months [27]20% non-small cell lung carcinoma (2nd-3rd line): 2.7 months [3, 28, 29]25% bladder cancer (1st-3rd line): 2.2 months [2, 30]15% head- and neck cancer (1st-2nd line): 2.0 months [31, 32]

We estimate to recruit 30% oligometastatic patients (defined as ≤3 metastases) and 70% non-oligometastatic (defined as > 3 metastases) in the trial. We hypothesize that an improved PFS of 3 months will be seen. We chose for a 36 month accrual time and a 12 month follow-up time. Analysis is planned 9 months after inclusion of the last patient.

Using these assumptions and including a 5% at random dropout rate, the trial requires a total of 98 patients to be randomized in to two groups. Sample size calculation was performed using R version 3.4.1.

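### Baseline quality of life is not secured before open-label allocation (text and tables disagree), and quality of life after the first evaluation will be sparse and, if SBRT works, selected differently by arm

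*Protocol article*

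**What the plan says.** QOL by QLQ-C30 is a secondary endpoint (Protocol article, Objectives). Its timing is fixed in two places.

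- **Text, Study calendar.** QOL appears in the list of baseline and pre-study evaluations, with this window: "Baseline evaluations are to be conducted within 2 weeks prior to start of checkpoint inhibitors". The schedule is then: "QOL will be assessed at baseline, at first evaluation and every 6 months thereafter".
- **Tables 1 to 3.** In all three, the row "Quality of life" is blank under Pre-study and first marked at C1D1. Allocation has its own earlier column, D-14 to -1. The close-out column, which holds the first imaging, is blank for QOL. The next mark is under the every-evaluation column, with the footnote "At least every 6 months".

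On blinding, the Evaluation and randomization section says: "As this is an open-label trial, the randomization procedure and outcome will not be blinded".

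On the end of visits, the text says "Patients will be followed up until disease progression defined as per iRECIST", and the table footnote to the every-evaluation column says "Consultation after imaging; until disease progression as per iRECIST". After confirmed progression only telephone contact for survival status is described.

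The Sample size section says: "Median PFS for the control arm was estimated at 3.1 months". It hypothesises a gain of 3 months.

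**The concern.** Two separate features weaken the QOL comparison.

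First, the baseline. The QLQ-C30 is self-reported and the arms are known. If it is completed at C1D1, as the tables schedule it, the patient can already know whether SBRT will follow, and relief or disappointment can enter the score. Change from baseline, or adjustment for baseline, would then use a covariate that the allocation itself may have affected. The text does not remove the problem, because its two-week window before the checkpoint inhibitor coincides with the allocation window and does not place the questionnaire before randomization.

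Second, the later assessments. After the first evaluation the required interval is long relative to the planned control PFS, and visits end at progression. The patients who supply later questionnaires are therefore chosen by the primary outcome. If SBRT lengthens PFS as hypothesised, that choice acts more strongly in the control arm, and the later comparison is no longer between the randomised groups. An analysis plan can address missing data, but it cannot recover a pre-allocation baseline or questionnaires that were never collected.

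**Working it through.** **Baseline timing, side by side**

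| Source | When baseline QOL is taken | Before allocation? |
|---|---|---|
| Text, Study calendar | Pre-study evaluation, within 2 weeks before the first checkpoint inhibitor dose | Not fixed: allocation falls in the same two weeks |
| Tables 1 to 3 | C1D1 | No: 1 to 14 days after allocation |

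Both readings put the questionnaire before SBRT and before or on the day of the first checkpoint inhibitor dose. Neither guarantees that it precedes knowledge of the arm.

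**Time of the first evaluation**

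- Nivolumab 2-weekly: C5D1 is 56 days after C1D1, and the window of +1 to +14 gives days 57 to 70. Nivolumab 4-weekly (C3D1) gives the same.
- 3-weekly drugs: C4D1 is 63 days after C1D1, and +5 to +20 gives days 68 to 83.
- Overall this is about 8 to 12 weeks after C1D1. Up to 14 more days from allocation gives at most 97 days.
- At 30.44 days per month the range is 57/30.44 = 1.9 to 97/30.44 = 3.2 months. I use 2.5 months as the central value, so the next required QOL is at 2.5 + 6 = 8.5 months.

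**Patients still progression-free**

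The plan gives no evaluable number or power for QOL, so there is no figure of its own to reproduce. Inputs: 98 patients randomised 1:1, hence 49 per arm; medians 3.1 and 3.1 + 3 = 6.1 months. Assumptions: exponential PFS, no other dropout, full questionnaire compliance.

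Formula: n(t) = 49 × 2^(−t/median).

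| Time (months) | Control | SBRT |
|---|---|---|
| 2.5, first evaluation | 49 × 2^(−2.5/3.1) = 28.0 (57%) | 49 × 2^(−2.5/6.1) = 36.9 (75%) |
| 5.5, existing 3-monthly evaluation | 49 × 2^(−5.5/3.1) = 14.3 | 49 × 2^(−5.5/6.1) = 26.2 |
| 8.5, next required QOL | 49 × 2^(−8.5/3.1) = 7.3 (15%) | 49 × 2^(−8.5/6.1) = 18.7 (38%) |

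Over the full range of first-evaluation times (1.9 to 3.2 months), the first evaluation has 24 to 32 control and 34 to 40 SBRT patients progression-free. Six months later (7.9 to 9.2 months) the counts are 6 to 8 and 17 to 20.

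**What those numbers can detect**

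Detectable difference in SD units, two-sided 5%, 80% power: (1.960 + 0.842) × √(1/n₁ + 1/n₂).

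- All randomised, 49 and 49: 2.802 × √(2/49) = 0.57 SD.
- First evaluation, 28 and 37: 2.802 × √(1/28 + 1/37) = 0.70 SD.
- 5.5 months, 14 and 26: 2.802 × √(1/14 + 1/26) = 0.93 SD.
- 8.5 months, 7 and 19: 2.802 × √(1/7 + 1/19) = 1.24 SD.

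**If SBRT had no effect on PFS**, both arms would have about 7 patients at 8.5 months. The sparsity would remain, but the difference in selection between arms would not follow from these figures.

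**The case against.** The strongest reply is that the plan already collects what is needed. The text requires QOL at the first evaluation, near the control median. Even counting only progression-free patients, about 28 and 37 contribute, and that understates the number: progression found on that scan does not prevent a questionnaire at the consultation that follows. The 6-month interval is only a minimum in the tables, so questionnaires at each 3-monthly evaluation are already allowed. Patients move to telephone follow-up only after confirmed progression, so iRECIST confirmation may keep some in visits longer. QOL is a secondary endpoint, questionnaire frequency trades information against burden, and the main time point and the handling of missing questionnaires may properly be left to an analysis plan.

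Most of this stands and it limits the point. A reader might infer that the whole QOL comparison rests on a handful of selected patients; the first-evaluation assessment shows that it does not. A reader might also infer that the baseline is always taken after allocation and is therefore biased. The documents do not support that either: the text leaves the order open, both arms start standard checkpoint inhibitors, and neither the size nor the direction of a reaction to allocation can be derived.

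The reply leaves three things untouched. Text and tables conflict on baseline timing, and neither version secures a questionnaire before allocation. A permitted extra questionnaire is not a required one. No QOL is described after confirmed progression.

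**Conclusion.** The point holds in two limited parts.

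1. **Baseline.** The text and Tables 1 to 3 disagree on when baseline QOL is taken. As the tables schedule it, the self-report follows open-label allocation and may be influenced by it. This is a risk, not a demonstrated bias.
2. **Later QOL.** The first-evaluation comparison is usable. At the next required assessment, about 8.5 months, roughly 7 of 49 control and 19 of 49 SBRT patients would be progression-free. A comparison there could detect only about 1.24 SD, and its two groups would have been filtered unequally by the primary outcome.

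The counts rest on exponential PFS, the plan's own medians, visits ending at progression, no other dropout and full compliance. Poorer compliance would lower them; delayed confirmation of progression would raise them somewhat. The unequal selection depends on the hypothesised PFS benefit, whereas the sparsity does not.

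**What to change.** - Reconcile the Study calendar text with Tables 1 to 3: mark the baseline QLQ-C30 under Pre-study and state that it is completed before allocation.
- Mark the first-evaluation questionnaire in a way that matches the text, since the close-out column is now blank for QOL.
- Require the questionnaire at each existing 3-monthly evaluation and at the visit where progression is recorded. Under the same assumptions the evaluation at about 5.5 months would add data from about 14 control and 26 SBRT patients.
- State that QOL comparisons beyond the first evaluation are descriptive. The choice of the main QOL time point can stay with the analysis plan.

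The cost is calendar wording and a few more questionnaires at visits that already take place, with a small added burden on patients and data entry. The change does not remove the selection: apart from the single questionnaire at progression, later QOL would still come mainly from non-progressors and in unequal numbers by arm.
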